### Experimental design

This study is designed as a three-arm randomized controlled trial. Given the limited number of longitudinal studies examining exercise interventions in esports, our sample size estimation was informed by the results of existing acute or short-term exercise studies aimed at enhancing esports performance, alongside preliminary data from our previous research [27,35]. Based on the effects of exercise on esports performance reported in these studies, we conservatively estimated a moderate effect size (d = 0.4) to power our primary outcomes (esports performance). Power analysis conducted via G*Power indicated that a minimum sample of 52 participants per group would be required to detect significant effects with 80% power (α = 0.05). Accounting for an anticipated dropout rate of 20%, 65 participants for each group will be recruited for this study. In total, we will recruit 195 participants, and they will be randomly allocated into three groups (1:1:1): HIIT, MICT, and a control group. To prevent baseline imbalances in variables relevant to gaming performance, a stratified block randomization procedure will be employed. Participants will be stratified into two strata based on their years of FPS gaming experience (e.g., above vs. below the median years of experience of the recruited cohort). Within each stratum, participants will be randomly allocated to the HIIT, MICT, or control group in a 1:1:1 ratio using randomly permuted blocks. The randomization sequence will be generated by an independent researcher using a computer-based random number generator (Research Randomizer) to ensure allocation concealment. The entire allocation process will be conducted by a staff member who will not be participating in the study. In scenarios requiring assessors to utilize measurement tools for evaluating metrics, we engage testers who are completely blind to the participants’ group assignments to conduct the assessments. For metrics tested via computer, our assessors serve merely to facilitate and oversee the process, with the computer’s saved data serving as the definitive record to ensure data objectivity. This approach has been proven reasonable in the past esports performance assessment [27]. The intervention groups will receive a 12-week HIIT or MICT exercise program, while the control group will not receive any intervention. All groups will report their dietary intake, physical activity, sleep patterns, and gaming activity. All participants will undergo a baseline test, followed by an immediate post-test at the end of the 12-week intervention period and a follow-up test 4 weeks after the intervention ends. Fig 2 illustrates the specific experimental procedure.

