### Measurements

To comprehensively evaluate the effects of the 12-week exercise intervention, the measurements in this study are systematically categorized into primary outcomes, secondary outcomes, exploratory outcomes, and control and monitoring variables. The core construct of our investigation is esports performance, which we conceptualize as a multidimensional framework comprising both objective operational skills and esports-related psychological skills. To implement our multidimensional evaluation of esports performance while maintaining strict statistical rigor, the primary outcome is specifically defined as flicking capacity in esports performance (quantified by the total number of targets successfully hit during a 1-minute task). This metric was strategically selected as the primary endpoint because it effectively captures “aiming throughput”, inherently accounting for the speed-accuracy trade-off by rewarding both speed and precision.

The secondary outcomes encompass the remaining dimensions of our esports performance framework, including other operational metrics (detection capacity, tracking performance, overall shooting accuracy, and reaction speed) and esports-related psychological skills, as well as body composition and physical competence.

Other outcomes were strategically selected to support and enhance the validity of our primary analysis while maintaining a clear focus on the main research objectives. These measures serve three specific purposes: (1) to identify and control for potential confounding variables through covariate analyses, ensuring robust assessment of the exercise’s effect on esports performance; (2) to monitor and standardize key lifestyle factors (e.g., sleep, affect, physical activity, and dietary intake) known to influence cognitive and gaming performance, thereby isolating the intervention effect; and (3) to enable supplementary analyses exploring potential mechanisms underlying the relationship between physical exercise and esports performance.

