#### Esports performance.

To comprehensively evaluate the objective operational skills, we utilized a specialized FPS training software called Aim Lab. Aim Lab is a free PC application designed to enhance aiming performance in FPS games. It offers comprehensive testing, training, and analysis features tailored to assess and improve players’ aiming abilities. Aim Lab has been employed in research on esports performance within the FPS gaming domain [68,69]. We selected five types of skill tests that are highly relevant to shooting games: flicking, tracking, accuracy, detection, and speed. Specifically, flicking capacity and detection capacity will be quantified by the total number of targets successfully hit during their respective 1-minute tasks. Tracking performance will be measured by the total time (in seconds) the participant successfully keeps the crosshair locked onto a moving target during the 1-minute tracking task. Furthermore, overall shooting accuracy and reaction speed will be evaluated. Accuracy will be calculated as the average hit rate (the percentage of successful hits out of total shots fired), while speed will be determined by the average reaction time (in milliseconds), with both metrics derived from the combined data of the flicking and detection tasks.

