Choosing to use a third-party shooting program for testing instead of a specific game's custom approach has several advantages. Firstly, it ensures that all shooting game players have the same level of familiarity with the testing program, preventing individual players from obtaining higher esports performance scores due to their proficiency in a chosen game. Secondly, Aim Lab is primarily a training program focused on practice rather than entertainment, and it is unlikely that casual players would engage in regular training with this program. By selecting this software, we can avoid the potential influence of players’ habitual use of Aim Lab during the 12-week intervention, which could enhance their proficiency and subsequently affect the final performance test. Additionally, we excluded habitual users of Aim Lab during the screening phase to mitigate this issue. On the other hand, using a specific mainstream shooting game for testing would make it difficult to control the spontaneous participation of players who are loyal users of those games during the 12-week intervention, leading to an increase in proficiency and potentially affecting the final game performance test. Furthermore, Aim Lab, being a dedicated shooting training and testing software, provides detailed test scores for different dimensions of shooting, such as reaction time and accuracy. Compared to previous studies that used custom modes within specific esports games for testing, using Aim Lab offers a more objective approach, avoiding subjective factors or errors dependent on assessors [27].

Before the Aim Lab test begins, each participant will undergo a warm-up session to familiarize themselves with the software, mouse, and keyboard setups. Razer Synapse will be used to help participants set the DPI (Dots per inch). All Aim Lab tests will be conducted on the same computer in our laboratory, using identical mouse and keyboard setups.

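### Assessor blinding is stated only for tool-based measures; the computer-run Aim Lab tests, including the primary flicking score, rely on the saved data, and their facilitating staff are not required to be blind

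*Protocol article*

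**What the plan says.** Experimental design in the Protocol article gives two rules for assessment.

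- Tool-based measures: "In scenarios requiring assessors to utilize measurement tools for evaluating metrics, we engage testers who are completely blind to the participants’ group assignments".
- Computer-run measures: "For metrics tested via computer, our assessors serve merely to facilitate and oversee the process". The protection offered for this class is the stored score: "with the computer’s saved data serving as the definitive record to ensure data objectivity". The article supports this approach by its use in an earlier esports study.

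Measurements names the endpoint: "the primary outcome is specifically defined as flicking capacity in esports performance (quantified by the total number of targets successfully hit during a 1-minute task". Esports performance identifies the instrument: "Aim Lab is a free PC application designed to enhance aiming performance in FPS games". The primary outcome is therefore a computer-run measure.

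Esports performance also describes what happens before the test. First, "each participant will undergo a warm-up session to familiarize themselves with the software, mouse, and keyboard setups". Second, "Razer Synapse will be used to help participants set the DPI". It adds that every Aim Lab test uses one laboratory computer with the same mouse and keyboard set-up.

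On participants, Weaknesses says that they cannot be blinded and mentions expectation bias for self-reported outcomes only.

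**The concern.** The article treats computer tests differently from tool-based tests and gives a reason: the computer keeps the record. That reason covers only what happens once the score exists. Staff contact comes earlier, during the warm-up inside the test software and while DPI is being set, and both could affect how many targets a participant hits in one minute.

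If facilitators know the allocation, they could give more practice or more careful set-up help to one arm at week 12 or 16 without meaning to. A difference between arms that arises only after baseline enters the group-by-time interaction, which Data analysis makes the test of the primary outcome. The GEE model cannot separate it from an effect of exercise.

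Group is easy to learn in this trial. Controls receive no intervention, research staff supervise the first three exercise sessions in the laboratory (Intervention), and dedicated researchers follow the Polar data and send repeated reminders (Strategies to improve adherence). Nothing in the article bars these people from running Aim Lab visits.

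**Working it through.** The article gives no figure on this point, so the check is mainly a reading of its rules.

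**Step 1. Which rule covers which outcome**

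| Outcome | How obtained | Rule that applies |
|---|---|---|
| Flicking capacity (primary) | Aim Lab | Computer: facilitation, saved data |
| Detection, tracking, accuracy, speed (secondary) | Aim Lab | Computer: facilitation, saved data |
| Body composition, physical competence (secondary) | Analyser, tape, dynamometer, field tests | Most naturally the tool rule: blind testers |
| Psychological skills (secondary) | Questionnaires | Self-report; tester blinding is not the main issue |

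The dividing line is tester-measured against software-scored. The primary outcome is on the software-scored side, together with four secondary outcomes.

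**Step 2. What each stated safeguard controls**

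| Safeguard | Controls | Does not control |
|---|---|---|
| Saved data as the record | Recording and scoring error | Anything done before the score is saved |
| Same computer, identical mouse and keyboard | Equipment differences | Staff conduct |
| Warm-up for every participant | Absence of familiarisation in one arm | Unequal amount, unless the warm-up is fixed |
| Interviews on expectancy (Perception) | Exercisers' views after week 12 | Handling of controls, or any difference in handling |

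None of these controls unequal warm-up or DPI help. Blinding of the facilitator would, and that is what the rule for computer tests leaves unstated.

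**Step 3. Scale, for illustration only**

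The documents give no bias figure. Let b be an assumed handling difference in SD units between one exercise arm and control, with no true effect and n per arm. For a simple two-sided comparison of two means at 5%,

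false-positive rate = P(|Z + b/√(2/n)| > 1.96).

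Inputs from Experimental design: n = 52 (after dropout) or 65 (recruited), and d = 0.4.

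Example, b = 0.20 and n = 52: √(2/52) = 0.196 and 0.20/0.196 = 1.02. The upper tail beyond 1.96 − 1.02 = 0.94 is about 0.174 and the lower tail about 0.001, together 0.175.

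| Assumed b | Share of d = 0.4 | Rate, n = 52 | Rate, n = 65 |
|---|---|---|---|
| 0 | 0% | 5.0% | 5.0% |
| 0.05 | 0.05/0.40 = 12.5% | 5.8% | 5.9% |
| 0.10 | 0.10/0.40 = 25% | 8.0% | 8.8% |
| 0.20 | 0.20/0.40 = 50% | 17.5% | 20.7% |

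The table shows how sensitive one exercise-versus-control contrast would be. It is no estimate of bias in this trial, and it simplifies the GEE analysis to two means.

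**The case against.** The strongest objection is that the article never calls the Aim Lab facilitators unblinded. They may be the same blinded testers mentioned one sentence earlier, and no text places the exercise supervisors or the staff who send reminders in the Aim Lab room. This stands. The point is only that the rule does not require blinding where it matters most.

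A reader might infer that the plan blinds the secondary outcomes and leaves the primary unblinded. The documents do not support that: four Aim Lab secondary outcomes fall under the same rule as the primary, and actual unblinding is not stated. A reader might also infer that staff encouragement would push scores, or that any bias must favour the exercise arms. The article describes no encouragement and no staff expectation, and for HIIT against MICT no direction is apparent.

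The score is a software count with no rater judgement, taken on standard equipment, which narrows the room for bias. That also stands, but it does not reach the staff contact before the test.

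Warm-up length and DPI handling may be set out in fuller procedures that a journal article leaves out. Their absence here is therefore no fault in itself. The reviewable part is the stated reasoning, which offers the saved data in place of blinding. The earlier study cited in support is not available here, so neither side can rest on it.

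Finally, blinding the facilitators would not touch the participants' own expectancy, which may be the larger source of bias. This is correct and limits what the fix can achieve.

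**Conclusion.** The concern holds in a limited form. As written, tester blinding is stated for tool-based measures only. For the primary flicking score and the other Aim Lab outcomes the plan relies on saved data and does not require blind facilitators. Saved data and common equipment protect scoring and hardware. They do not protect against unequal warm-up or DPI help by staff who may know the group.

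The size of any bias cannot be estimated from the document; the 0.05 to 0.20 SD range is an assumption that shows scale. The conclusion rests on two premises: that facilitators could know the group, which the text permits but does not assert, and that warm-up and set-up can affect a 1-minute aiming score. If the facilitators are in fact the blinded testers, one sentence settles the blinding part. The change is worth making because it is cheap and concerns the primary endpoint, but the trial does not stand or fall by it.

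**What to change.** Amend Experimental design so that the blinding rule also covers Aim Lab.

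- Aim Lab sessions, at least at weeks 12 and 16, are run by the blinded testers already engaged. Failing that, they are run by staff with no role in exercise supervision, Polar monitoring or reminders.
- Participants are asked not to reveal their group to the tester.
- The warm-up is the same and of fixed length for everyone at every visit.
- Each participant's DPI is recorded at baseline and held at that value afterwards.

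If the fuller procedures already contain the last two items, a reference to them is enough.

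In Weaknesses, extend the acknowledged expectation bias from self-reported outcomes to the performance test, since the changes above leave participants' own expectancy in place.

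The cost is rostering of existing staff, a short written procedure and somewhat less flexible scheduling of Aim Lab visits. The change must be in place before the week 12 visits begin, because unequal handling cannot be corrected in the analysis.

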
**Fig 2 pone.0357119.g002:**
[figure not shown]
Flow chart of the experimental procedure.

### Measurements

To comprehensively evaluate the effects of the 12-week exercise intervention, the measurements in this study are systematically categorized into primary outcomes, secondary outcomes, exploratory outcomes, and control and monitoring variables. The core construct of our investigation is esports performance, which we conceptualize as a multidimensional framework comprising both objective operational skills and esports-related psychological skills. To implement our multidimensional evaluation of esports performance while maintaining strict statistical rigor, the primary outcome is specifically defined as flicking capacity in esports performance (quantified by the total number of targets successfully hit during a 1-minute task). This metric was strategically selected as the primary endpoint because it effectively captures “aiming throughput”, inherently accounting for the speed-accuracy trade-off by rewarding both speed and precision.

The secondary outcomes encompass the remaining dimensions of our esports performance framework, including other operational metrics (detection capacity, tracking performance, overall shooting accuracy, and reaction speed) and esports-related psychological skills, as well as body composition and physical competence.

Other outcomes were strategically selected to support and enhance the validity of our primary analysis while maintaining a clear focus on the main research objectives. These measures serve three specific purposes: (1) to identify and control for potential confounding variables through covariate analyses, ensuring robust assessment of the exercise’s effect on esports performance; (2) to monitor and standardize key lifestyle factors (e.g., sleep, affect, physical activity, and dietary intake) known to influence cognitive and gaming performance, thereby isolating the intervention effect; and (3) to enable supplementary analyses exploring potential mechanisms underlying the relationship between physical exercise and esports performance.

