### Participants

We will recruit healthy adult FPS gamers of any gender for this study through the university’s mass mail websites and social media platforms such as WeChat groups, and Instagram. Additionally, the QR code for the initial online survey will be displayed at offline esports activities for anyone interested in participating. The age range of participants will be set between 18 and 29 years for two reasons: firstly, this age range represents the primary demographic of current esports participants and professional esports athletes [61,62]; Secondly, setting the age limit at 18 is also in consideration of the regulations of the Chinese National Radio and Television Administration regarding the participation of minors in video games. Under the regulations of the National Radio and Television Administration and the implementation of the Chinese Online Game Fatigue System in games, minors have limited opportunities to engage in esports gaming [63]. Therefore, in compliance with national regulations and for the protection of minors, participants under the age of 18 will not be recruited in this study. As for the determination of esports players, based on previous literature, we will recruit players who have engaged in esports games within the past six months [32,62,64]. In summary, our inclusion and exclusion criteria are as follows:

Inclusion criteria:

18–29 years old;regular FPS players with at least 1 year of FPS gaming experience, who have played FPS games for a minimum of 5 hours per week over the past six months [27];healthy individuals who are capable of physical exercise and tests, assessed and confirmedby the Physical Activity Readiness Questionnaire (PAR-Q) [65];no regular exercise habits (engaging in < 2 structured exercise sessions per week) [66,67];can understand English or Chinese.

Exclusion criteria:

self-reported history of neurological, psychiatric, or medical diseases;having heart disease, hypertension, musculoskeletal injuries, or any other conditions that pose a risk to engaging in physical activitycurrent intake of medications and/or recreational drugs that could affect the central nervous system and/or the ability to learn;a regular user of Aim Lab (used Aim Lab more than once a week in the past six weeks), to prevent baseline bias and potential learning effects, as Aim Lab will be utilized as the primary training and assessment tool in our subsequent intervention.

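### The primary outcome reads as one 1-minute run per visit: averaging three runs would cheaply buy precision, and the equal-familiarity claim does not match the eligibility rule

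*Protocol article*

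**What the plan says.** The protocol article names one primary outcome, flicking capacity, "quantified by the total number of targets successfully hit during a 1-minute task" (Measurements). The section on esports performance repeats the definition: "Specifically, flicking capacity and detection capacity will be quantified by the total number of targets successfully hit during their respective 1-minute tasks". Neither place gives a number of runs or a rule for averaging or choosing among them. Accuracy and reaction speed, both secondary, are averages over the pooled flicking and detection data.

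On familiarity, the same section argues for a third-party program because "it ensures that all shooting game players have the same level of familiarity with the testing program". The exclusion criterion under Participants removes only "a regular user of Aim Lab (used Aim Lab more than once a week in the past six weeks".

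On preparation and equipment, "Before the Aim Lab test begins, each participant will undergo a warm-up session to familiarize themselves with the software, mouse, and keyboard setups". The article adds that "Razer Synapse will be used to help participants set the DPI (Dots per inch", and that "All Aim Lab tests will be conducted on the same computer in our laboratory, using identical mouse and keyboard setups".

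All arms are tested at baseline, week 12 and week 16. The effect is tested as a group-by-time interaction in a GEE model (Data analysis).

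**The concern.** A count from a single minute of play varies from run to run even when skill is unchanged. If one run is the whole score, that variation enters the primary outcome at all three visits and widens the standard error of every contrast. It also inflates the variance of individual change. Data analysis relies on that variance twice: it is compared between groups to detect true differences in response, and it underlies the planned correlations between performance and fitness measures, which noise attenuates.

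Differing exposure to the program adds to this. Someone who used Aim Lab once a week, or daily until seven weeks ago, is eligible alongside someone who has never opened it. For one, baseline is a practised score; for the other, it may be among the first attempts. Their later gains will then differ for reasons unrelated to exercise. Stratification is by years of FPS experience, not by Aim Lab use, so it does not address this directly.

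**Working it through.** **Inputs from the article (Experimental design; Data analysis).** d = 0.4, 80% power, α = 0.05 (two-sided for the primary outcome), 52 per group, 20% dropout, 65 recruited per group. No SD and no reliability is given, so single-run reliability r is an assumption, shown at 0.6, 0.7 and 0.8.

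**The plan's own figure.** 52/(1 − 0.20) = 65, as stated. The 52 itself is reproduced by a paired t-test at d = 0.4 (51.01, rounded up). Comparing two arms at one visit needs n = 2(1.960 + 0.842)²/0.4² = 98.1, so 99 per arm. With 52 per arm, power is Φ(0.4 × √26 − 1.960) = Φ(0.080) = 53%. The basis of the 52 is a separate and larger question. Here these numbers serve only as a reference.

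**Step 1: does shared learning bias the effect?** Let every participant gain L between visits. The difference in mean change between arms is (effect + L) − L = effect. A simulation with 52 per arm, true-score SD 1, run-error SD 0.65 and a true effect of 0.40 gave a mean estimate of 0.40 both with L = 0 and with L = 1. The SE was 0.18 in both, matching √(2 × 2 × 0.65²/52) = √0.0325 = 0.18. If individual gains vary with variance s², the variance of change becomes 2 × 0.65² + s². The estimate stays unbiased but its SE grows. The article offers nothing from which to set s.

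**Step 2: what is averaging three runs worth?** Spearman-Brown: r₃ = 3r/(1 + 2r). The sample-size equivalent when arms are compared at one visit is r₃/r = 3/(1 + 2r). If d = 0.4 refers to a single-run score, three runs give d = 0.4 × √(r₃/r).

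| r | r₃ | r₃/r | d, three runs | n per arm, 80% power | power at 52 per arm |
|---|---|---|---|---|---|
| 0.6 | 0.818 | 1.36 | 0.467 | 72 | 66% |
| 0.7 | 0.875 | 1.25 | 0.447 | 79 | 63% |
| 0.8 | 0.923 | 1.15 | 0.430 | 86 | 59% |

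The single-run reference is 99 per arm and 53%.

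If d = 0.4 instead refers to error-free skill, one run gives d = 0.4 × √r = 0.310, 0.335, 0.358 and power of 35%, 40%, 45% at 52 per arm. Three runs give d = 0.362, 0.374, 0.384 and power of 45%, 48%, 50%.

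**Step 3: limits of the figures.** Spearman-Brown treats all error as independent between runs. Three runs in one session do not remove day-to-day variation or individual learning over 12 weeks. If the assumed unreliability includes these, the gain is smaller. The table also concerns a single visit. In a change-from-baseline contrast the gain depends in addition on the correlation between visits, which the article does not give, so no figure is put on it.

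**Step 4: side effect of repeating only flicking.** Accuracy and speed pool both tasks. With one run each, flicking supplies 1 of 2 runs; with three flicking runs and one detection run it supplies 3 of 4.

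**The case against.** The strongest reply is that a condensed article gives the unit of the score and leaves the number of runs, the content of the warm-up and the carry-over of settings to the full protocol. This largely stands for the warm-up and for DPI, which are details to state rather than errors. It stands only in part for the number of runs. The endpoint definition is given twice, as a count from one task, while averages are named where they are meant. If repeat runs are already planned, one sentence settles the matter.

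A reader might infer several stronger points that the article does not support:

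- That participants get no practice before baseline. The article provides a warm-up in which "each participant will undergo a warm-up session to familiarize themselves with the software, mouse, and keyboard setups". What it does not say is whether this includes full runs of the scored task, or how many.
- That most participants are new to Aim Lab. Only frequent recent users are excluded, and the mix of the rest is unknown.
- That learning distorts the week 12 and week 16 effects. Shared learning cancels (Step 1). Only learning that differs by arm would bias, and only learning that differs between people adds noise.
- That the week 16 objective suffers most. The same measurement noise applies at both visits.
- That DPI will drift between visits. The article specifies identical mouse and keyboard setups and does not say that DPI may change, although it does not tie DPI to the baseline value either.

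It is also fair to say that if d = 0.4 already describes a single-run score, the design loses nothing further. Averaging is then a gain, not the repair of a shortfall.

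**Conclusion.** The point holds as a cheap gain in precision plus one incorrect statement; the validity of the comparison is not at stake. As written, the primary outcome is a single 60-second count per visit, so run-to-run noise enters each score. For assumed within-session reliability of 0.6, 0.7 or 0.8 with independent run errors, the mean of three runs is worth at most about 36%, 25% or 15% more participants in a comparison of arms at one visit, and less where day-to-day variation or individual learning makes up part of the error. The true size cannot be derived from the article.

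The statement that the software secures equal familiarity is contradicted by the exclusion criterion, which admits occasional and lapsed users. The consequence is possible extra between-person variance in change, of unknown size.

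The absence of bias assumes that Aim Lab practice is the same in all arms. The Intervention section describes exercise only, but the exclusion criterion calls Aim Lab a training tool as well as an assessment tool. Those passages should be reconciled.

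**What to change.** - Define flicking capacity at every visit as the mean of three scored 1-minute runs with short rests between them.
- Have the existing warm-up include the same fixed number of unscored full flicking runs for every participant.
- Record each participant's DPI and in-program sensitivity at baseline and keep them at weeks 12 and 16.
- Record prior Aim Lab use at screening and delete the equal-familiarity claim.
- Compute accuracy and reaction speed so that flicking and detection keep their planned weights, for example by repeating both tasks equally or by averaging per-task means.

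The cost is 2 extra scored minutes per visit (4 if detection is repeated too), plus rests and the warm-up runs, on the same computer with the same staff. The downside is slight hand fatigue, which the rests limit. No extra participants are needed.
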